### Measures taken to minimize/avoid bias, including randomization and blinding

#### Randomization

Patients who meet the inclusion criteria and agree to participate in the study are randomly assigned to one of the two therapy arms either CAMS (36 subjects) or TAU (36 subjects). Randomization is performed by an independent practitioner by throwing the dice immediately after the patients have agreed to participate in the study and returned the completed questionnaires (1–3 = CAMS, 4–6 = E-TAU).

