#### Treatment fidelity

The therapists in CAMS and TAU are a licensed psychotherapist and a psychologist (Msc.). The assignment to the therapist is consecutive, i.e. the clinician who conducted the admission interview will also be responsible for further treatment. Potential effects of the therapists will be analysed during the evaluation and using post-hoc analyses. We trained CAMS therapists with help of the E-learning training by [name], which both therapists have completed before the start of the study. Additionally, both have worked intensively with the CAMS manual written by [name]. The administration of the Suicide Status Form (SSF) was practiced by each therapist with at least 3 patients in a pilot phase prior to the start of the study. This methodology ensured that the therapists internalized both the content and process of CAMS demonstrating sufficient adherence to the CAMS framework. In the event of difficulties, [name] provides consultation.

Every fourth treatment session of the therapists is supervised. Each therapy session is audiotaped, and the therapists are rated for adherence according to the CAMS Rating Scale (CRS) by an external evaluator so optimal treatment adherence to CAMS is ensured [46]. The supervisors also monitored the E-TAU sessions using the CRS to ensure and verify that clinicians were not doing CAMS procedures in these sessions thus ensuring experimental fidelity. The CRS is an observer rating scale and consists of three parts and 14 items in total. Part I covers the treatment philosophy, part 2 the clinical/ session framework and part 3 the overall rating. The items were rated on a 6-point scale from 0 = poor to 6 = excellent. The use of the CRS therefore serves to confirm the difference in treatment groups with regard to the fact that the same therapists are treating both groups. We discussed the problem of the CAMS therapists being also the TAU therapists and the question if how the therapy is influenced by the knowledge about the other therapy arm. But in fact, despite the risk of contamination were mitigated by review of videos and use of the CRS. Any experimental between-group differences would provide clear proof of an experimental effect as the clinicians serve as their own control (removing a tremendous source of error variance seen in other RCT’s that use different clinicians in each arm of the trial).

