**Table Taba:** 

Version	Author	Date	Reason for Revision
0.1	[name]	1 March 2019	1st draft version sent to participating authors for review
0.2	[name]	24 May 2019	2nd draft version with integrated feedback from all co-authors sent to all co-authors again
1.1	[name]	29 May 2019	1st version sent for review
1.2	[name]	March 2020	2 ^nd^ revised version

Date: 29 May 2019

The trial opened by recruiting the first patient on 8 March 2017 and is still recruiting. Recruitment is terminated when the targeted number of 30 patients in each treatment group has been reached. Recruitment is expected to be completed in autumn 2019.

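### Unrestricted die throws cannot secure the stated arm sizes and leave no pre-set sequence to check an allocation against

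*Protocol article*

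**What the plan says.** The Randomization section says patients are "randomly assigned to one of the two therapy arms either CAMS (36 subjects) or TAU (36 subjects"). The next sentence gives the mechanism: "Randomization is performed by an independent practitioner by throwing the dice immediately after the patients have agreed to participate in the study" and have "returned the completed questionnaires". The key is "1–3 = CAMS, 4–6 = E-TAU", so each patient has probability 3/6 for either arm. No blocking, stratification or pre-generated sequence is mentioned.

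The sample size section likewise derives 72 randomised, 36 per group, from a target of 30 per group. The Trial status section has a different end point: "Recruitment is terminated when the targeted number of 30 patients in each treatment group has been reached".

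Under Treatment fidelity, "The therapists in CAMS and TAU are a licensed psychotherapist and a psychologist (Msc"). Both therapists treat both arms. "The assignment to the therapist is consecutive": whoever held the admission interview also treats the patient. Therapist effects are left to post-hoc analyses. The Blinding section says that participants and therapists cannot be blinded. The primary outcome, the Beck Scale for Suicide Ideation, is a self-report instrument.

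**The concern.** There are two separate problems.

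**Method and targets do not match.** A die thrown afresh for each patient fixes the probability of each arm, not the count. The article nevertheless states exact counts for the arms and a stopping rule in terms of both arms. It does not say what happens when the throws run unevenly. If throwing continues until both arms reach 30, the total randomised is a random number. If throwing stops once one arm is full at 36, the remaining patients have a known allocation.

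**An allocation cannot be checked.** With a list prepared in advance, every allocation can be compared with the entry that was due. A die has no such reference. A log of throws shows the results that were accepted; it cannot show that a throw was repeated. Therapists and patients know the arm, the therapist who admits also treats, and the primary outcome is the patient's own report. In that setting a checkable allocation is one of the few safeguards against doubt about selection, and a sceptical reader could not be answered.

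**Working it through.** **Inputs.** From the article: probability 0.5 per arm; 72 planned, stated as 36 and 36; stopping target 30 per arm (60); two therapists, both treating both arms. Assumed: a fair die, independent throws, and, for the therapist figures only, an equal split of patients between the two therapists, because the article gives none.

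**1. Chance of the stated split.** P(exactly m:m of 2m) = C(2m, m) / 2^(2m).
- m = 36: 0.0937, or 9.4%.
- m = 30: 0.1026, or 10.3%.

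**2. Size of the imbalance.** X ~ Binomial(72, 0.5).
- The central 95% range for one arm is 28 to 44.
- P(30:42 or worse) = 2 × P(X ≤ 30) = 0.1945, or 19.5%.

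**3. Total randomised if throwing continues until both arms hold m.** After 2m throws the smaller arm lacks |X − m| patients, and each missing patient needs two further throws on average. Since E|X − m| = m × C(2m, m) / 2^(2m), the mean total is 2m × [1 + C(2m, m) / 2^(2m)].
- m = 30: 60 × 1.1026 = 66.2. A simulation of 50,000 trials gave 66.1, with a 95th percentile of 77.
- m = 36: 72 × 1.0937 = 78.7.
- P(more than 72 needed for 30 in each arm) = 1 − P(30 ≤ X ≤ 42 of 72) = 1 − 0.8751 = 0.125, or about 12%.

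This counts patients as allocated. If the target of 30 counts only patients retained, and 20% are lost as the sample size section assumes, the mean number randomised becomes 66.2 / 0.8 = 82.7.

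**4. If throwing stops once one arm has 36 of 72.** The throws at which the first and the second arm fill have means summing to 2 × 72 = 144. The second has mean 78.7, so the first has 65.3. On average about 72 − 65.3 = 6.7 patients then have a predetermined arm.

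**5. Effect on power.** Efficiency relative to equal arms is 4·n1·n2 / N².
- 30:42: 4 × 30 × 42 / 72² = 0.972.
- 28:44: 4 × 28 × 44 / 72² = 0.951. Two-sided power at d = 1 is 98.3%, against 98.7% for 36:36.

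**6. Therapist.** The share of patients given CAMS differs between the two therapists by 20 points or more in 15.5% of trials with 30 patients each and in 7.6% with 36 each. The range is therefore about 8 to 16%, depending on the assumed numbers.

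**7. What restriction costs in predictability.** Someone who knows all past allocations in a list and always guesses the lagging arm is right, per block of 2m, in a share [m + 0.5 × 2^(2m) / C(2m, m) − 0.5] / (2m).
- Blocks of 4 (m = 2): (2 + 1.333 − 0.5) / 4 = 70.8%.
- Random blocks of 4 and 6: about 69% by simulation.
- One list with fixed totals 36 + 36 (m = 36): (36 + 0.5 / 0.0937 − 0.5) / 72 = 40.8 / 72 = 56.7%.
- Dice: 50%.

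Therapist-stratified blocks of 4, or of 4 and 6, would give exactly 36:36 in 61% and 55% of trials, and a difference of at most 2 patients in about 98%.

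**The case against.** The strongest defence is that simple randomisation by an independent person, after consent and completed baseline questionnaires, is valid and gives no clue to the next allocation. That is correct. On unpredictability the die beats any blocked list. The usual remedy, small random blocks stratified by therapist, would give each unblinded therapist, who also does the admission interviews, the very sequence needed to guess about 69% of the next allocations. Random block sizes do not remove this. The point stands, and it shapes the fix.

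A second defence is that 36 per arm is only a planning expectation, and that 30 per arm can be reached by continuing to throw, within 72 patients in 87.5% of cases. This too is fair. It means that the wording and the stopping rule need repair; it does not make the target unreachable.

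Third, a condensed article may omit whether throws were logged or witnessed. So the absence of a log is not held against the plan. What remains is a property of the method as described: even a complete log does not supply a sequence set beforehand.

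A reader might also infer that the dice break a promise of balance by therapist, that they tie arm to therapist, or that they seriously weaken the trial. The documents do not support these readings. Balance by therapist is never promised, both therapists treat both arms, and an imbalance in shares can be handled in the model. Section 5 of the working shows the loss of power to be minor. Nor does the article place the throw on the ward or describe it as unobserved.

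**Conclusion.** The point holds in a limited form. The allocation is true randomisation, but it is inconsistent with the fixed arm sizes printed beside it and leaves the total randomised to chance under the rule in Trial status. Exact 36:36 arises in 9.4% of trials, 30:42 or worse in 19.5%, and reaching 30 in both arms takes about 66 patients on average and more than 72 in about 12%. These figures rest on a fair die, independent throws and the 30 counting allocated patients. The more important weakness cannot be put as a percentage: there is no pre-set sequence against which to check an allocation, so a repeated throw would go undetected. Nothing in the article suggests that any throw was repeated. A change is worthwhile because it is cheap and makes allocation verifiable; gains in power or therapist balance are not the reason.

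**What to change.** 1. For any remaining allocations, replace the die with a computer-generated list prepared in advance and held concealed by a person uninvolved in treatment. Release each entry only after consent and t1 are logged.
2. Restrict the list only loosely over the whole trial: one list with fixed totals, or large varying blocks. Avoid small therapist-stratified blocks.
3. Stop at a fixed total randomised, and say whether the targets of 36 and 30 count patients randomised or retained. Reconcile the Randomization, sample size and Trial status sections accordingly, stating arm sizes as approximate for patients already allocated by die.
4. Include therapist as a covariate in the mixed model instead of leaving it to post-hoc analysis.
5. Archive the date, therapist and arm of every past throw, and report in the publication that dice were used and for which patients.

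The cost is a protocol amendment, about an hour to generate the list, two allocation methods within one trial, and somewhat more predictability than dice (56.7% against 50% for a fixed-total list of 72, for someone who sees every allocation). Trial status expected recruitment to finish in autumn 2019, so items 1 and 2 may affect few or no patients. Items 4 and 5 and the reconciliation in item 3 are useful in any case, but they cannot make past throws verifiable.

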#### Blinding

Due to the behavioral nature of the intervention, neither participants nor therapists and therapy interpreters can be blinded. However, the diagnostic examination is performed by an independent clinician who is blinded for the study group and we tried to keep the group membership confidential from the treatment team and from other patients and study participants, e.g. there was no documentation about the group membership in the patient file. Participants are instructed not to reveal any information related to the group they have been assigned to or regarding the therapeutic process.

#### Trial monitoring

There are regular appointments with the supervisors once a month with the main purpose to observe the progress, the well-being of the patients and to identify problems in conducting the study and to solve problems together. Supervisors have access to all documents (e.g. assessments, audiotapes of therapy sessions, therapy session sheets) to check diagnostic accuracy, consistency of data entry, and adherence to treatment.

#### Treatment fidelity

The therapists in CAMS and TAU are a licensed psychotherapist and a psychologist (Msc.). The assignment to the therapist is consecutive, i.e. the clinician who conducted the admission interview will also be responsible for further treatment. Potential effects of the therapists will be analysed during the evaluation and using post-hoc analyses. We trained CAMS therapists with help of the E-learning training by [name], which both therapists have completed before the start of the study. Additionally, both have worked intensively with the CAMS manual written by [name]. The administration of the Suicide Status Form (SSF) was practiced by each therapist with at least 3 patients in a pilot phase prior to the start of the study. This methodology ensured that the therapists internalized both the content and process of CAMS demonstrating sufficient adherence to the CAMS framework. In the event of difficulties, [name] provides consultation.

Every fourth treatment session of the therapists is supervised. Each therapy session is audiotaped, and the therapists are rated for adherence according to the CAMS Rating Scale (CRS) by an external evaluator so optimal treatment adherence to CAMS is ensured [46]. The supervisors also monitored the E-TAU sessions using the CRS to ensure and verify that clinicians were not doing CAMS procedures in these sessions thus ensuring experimental fidelity. The CRS is an observer rating scale and consists of three parts and 14 items in total. Part I covers the treatment philosophy, part 2 the clinical/ session framework and part 3 the overall rating. The items were rated on a 6-point scale from 0 = poor to 6 = excellent. The use of the CRS therefore serves to confirm the difference in treatment groups with regard to the fact that the same therapists are treating both groups. We discussed the problem of the CAMS therapists being also the TAU therapists and the question if how the therapy is influenced by the knowledge about the other therapy arm. But in fact, despite the risk of contamination were mitigated by review of videos and use of the CRS. Any experimental between-group differences would provide clear proof of an experimental effect as the clinicians serve as their own control (removing a tremendous source of error variance seen in other RCT’s that use different clinicians in each arm of the trial).

#### Treatment feasibility

The feasibility of the measures is assessed on the basis of dropout rates and the satisfaction with the assigned procedure is also measured. A therapy dropout is operationally defined if the treatment is terminated before the conclusion of at least 3 sessions.

### Measures taken to avoid attrition bias

In order to prevent an attrition bias, we will endeavour to examine patients even after a discontinuation of the study participation (and will conduct our analyses based on intention to treat methodology). In order to estimate the extent of a possible bias, the participants who remain in the study will be compared with those who drop out prematurely. Because we expect some difficulties in collecting follow-up data (for which patients are expected to return to the clinic after discharge), a small expense allowance of 10 Euros for their travel expenses will be offered to reduce any attrition bias due to systematic dropouts.

### Data handling and quality control

Our clinic is responsible for handling of the data generated in our institution according to the General Data Protection Regulation (GDPR). Data storage and transfer will be conducted exclusively in an encrypted manner. Three different kinds of data will be produced at the centers: (1) Personal data including names and contact information, (2), screening, diagnostic, and therapy process data (using pseudonyms for participants), and (3) source data (e.g., audios of assessments and therapy sessions, therapy session sheets). A separate code list with a unique identifier for each participant links the personal data and our use of pseudonyms. The code list is securely stored at the clinic and will be deleted at the end of the project duration. We will transfer the disguised and encrypted data to a secure server accessible only to authorized staff. Checks for completeness will be conducted to ensure data integrity. Statistical analyses will be conducted by independent collaborators. Direct access to trial documents, including source data, is provided for trial-related monitoring and reviews by the ethical committee or regulatory authorities if requested following the guidelines of the GDPR. All individuals who are authorized to perform the aforementioned reviews are bound to confidentiality.

### Statistics

#### Power analysis and sample size calculation

An a priori power analysis by using G*Power was carried out to determine the sample size [47]. On the basis of the available literature, we expect an average effect size (comparison of CAMS versus TAU with regard to the reduction of suicidal tendencies) of Cohen’s d = 1. Here we refer to the study by Ellis (2015), which is rather comparable [21]. The author reports a pre-post effect size of d = 1.72 for CAMS (measured by the BSS) and of d = 0.71 for TAU. Although the interaction effect was not reported we assume it to be about d = 1.

Taking into account a probability of α error = 5% (one-sided) and a power of 1 - β = 80%, the total sample size of 48 participants, i.e. 24 per group. For compensating participants who withdraw their consent we plan 30 subjects per group. Assuming that after the first diagnostic examination 50% are not eligible for inclusion into the study due to non-existent inclusion criteria or exclusion criteria and 20% discontinue treatment in the course of the study or are excluded due to further inpatient treatment, it is to be expected, that 144 patients have to be interviewed, of whose 72 patients (36 per group) are randomly assigned to CAMS intervention (36 subjects) and a TAU (36 subjects), respectively, in order to achieve the targeted number of *N* = 2 × 30 in the intent to treat sample.

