### Data analyses

#### Statistical analyses

The analysis of this study will be calculated as a mixed-effects model with the BSS total symptom score as the outcome variable. Mixed models are especially suited for longitudinal studies as they can deal with a correlated data structure and can analyze all cases and data points, even if missing values occur in the course of the trial. In detail, participants will be modeled as a random factor, while time and intervention (CAMS vs. TAU) as well their interaction will be modeled as fixed factors. The hypothesis that CAMS is superior to TAU in the treatment of suicidal patients will be evaluated by the significance test of the interaction effect time × intervention.

In case of a significant interaction effect, two planned general linear hypotheses will be calculated as post-hoc tests for linear mixed effect models in order to test between-group differences at t_2_ and t_3_. *P*-values will be adjusted for multiple comparisons following the Holm procedure.

We will perform an intention-to-treat analyses, that is, all trial participants will be analyzed as randomized, even if they discontinue treatment or are unavailable for one or both of the follow-up interviews. The between-group effect size (Cohen’s d) will be calculated at each follow-up assessment (t_2_ and t_3_).

Continuous secondary outcome measures (BDI-II, SCL-18-Mini, B-RFL, D-STAR-P) are analyzed in the same way. In absence of a valid cut-off score for clinically significant change or treatment response of the BSS, the number of subjects with clinically significant improvement as well as worsening based on the reliable change index (RCI) will be compared between groups using χ2 –tests or Fisher’s exact tests. For this purpose, the RCI will be calculated based on the pre-treatment scores of the study sample. We will use two-tailed tests for statistical significance with alpha set at *P* < 0.05. Effect strength will be determined with Cohen’s d. All calculations will be performed using SPSS 20.0 computer software [48].

We also investigate whether there is a correlation between the number of sessions and the effect of the therapeutic treatment using a correlation analysis.

Interim analyses before the completion of the investigations are not intended. Any potential deviations from the original statistical plan as defined in the study protocol will be described in protocol amendments as well as in the final study report.

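### The 24 per group does not follow from d = 1, one-sided 5% and 80% power, the one-sided alpha contradicts the two-tailed analysis, and these inputs cannot give power for the interaction test

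*Protocol article*

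**What the plan says.** All references are to the protocol article.

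- **Power analysis and sample size calculation.** G*Power was used, but the procedure run in it is not named. The effect size comes from one earlier study, which "reports a pre-post effect size of d = 1.72 for CAMS (measured by the BSS) and of d = 0.71 for TAU". The text continues: "Although the interaction effect was not reported we assume it to be about d = 1". It sets a "probability of α error = 5% (one-sided") and "a power of 1 - β = 80" per cent, and concludes with "the total sample size of 48 participants, i.e. 24 per group". It then adds: "For compensating participants who withdraw their consent we plan 30 subjects per group".
- **Statistical analyses.** The outcome is analysed in a mixed-effects model with participant as a random factor, and time, intervention and their interaction as fixed factors. Superiority of CAMS "will be evaluated by the significance test of the interaction effect" of time and intervention. On sidedness the section says: "We will use two-tailed tests for statistical significance with alpha set at" 0.05. No one-sided test is announced for the primary outcome.
- **Primary outcome and Trial design.** The BSS is taken at four assessments, t1 to t4.

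**The concern.** The power section is the only justification given for the trial's size, and the 30 per group, the 60, the 72 and the 144 all build on the 24. Three things do not fit together.

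1. The stated effect size, alpha and power should produce a much smaller number than 24.
2. The trial is sized one-sided and analysed two-tailed. While both statements stand, a reader cannot tell which threshold a result near the boundary has to meet.
3. The deciding test is an interaction with time as a factor. Its power depends on the number of measurements, their correlation and the pattern of the difference over time, and none of these is tied to the calculation.

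What is at stake is interpretation. A null result would be read against d = 1 with 80% power, which does not describe a trial with 24 or 30 per arm tested two-sided. The Discussion warns that only a large effect could be detected, but a reader cannot work out from the power section how large.

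**Working it through.** **Inputs from the power section.** d = 1 (from 1.72 − 0.71 = 1.01); alpha 0.05 one-sided; power 0.80; equal allocation; stated result 24 per group.

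**Step 1: try to reproduce 24.** For two means, the normal approximation is n per group = 2(z₁₋α + z₁₋β)²/d².

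- One-sided: 2(1.645 + 0.842)² = 12.4, so 13.
- Two-sided: 2(1.960 + 0.842)² = 15.7, so 16.

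The exact calculation for a two-sample t-test uses the noncentral t with 2n − 2 degrees of freedom and noncentrality d√(n/2). It gives **14** per group one-sided (28 in total) and **17** two-sided (34 in total). Using 1.01 instead of 1 gives 13 and 17. The stated 24 is not reproduced, and the difference in sidedness does not explain it.

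**Step 2: what 24 and 30 per group would give** (exact t; at 24 per group the noncentrality for d = 1 is √12 = 3.46 on 46 df).

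| | 24 per group | 30 per group |
|---|---|---|
| Power at d = 1, one-sided 5% | 96.1% | 98.5% |
| Power at d = 1, two-sided 5% | 92.4% | 96.8% |
| d detectable with 80% power, one-sided | 0.73 | 0.65 |
| d detectable with 80% power, two-sided | 0.83 | 0.74 |

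**Step 3: look for inputs that would give about 24.** Results near 24 appear only with values that the article does not state:

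- 95% power one-sided: 23 per group.
- 90% power two-sided: 23 per group.
- Alpha of 0.01: 22 per group one-sided, 26 two-sided.
- d = 1 in raw SD units with a change score, where d for change = 1/√(2(1 − ρ)): at ρ = 0 this is 0.71 and needs 26 one-sided; at ρ = 0.25 it is 0.82 and needs 25 two-sided.
- A repeated-measures interaction with f = 0.25, four measurements and zero correlation: 46 in total.

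Several different slips or omissions could therefore lie behind the figure, and the text does not allow a choice between them. The next step is consistent with a 20% allowance: 24/0.8 = 30. The break is at the 24.

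**Step 4: why the inputs do not fix power for the deciding test.** If all four assessments enter as a factor, the interaction has 3 numerator degrees of freedom and no one-sided form. Under compound symmetry the noncentrality is λ = (n/2) Σ(δⱼ − δ̄)²/(1 − ρ), where δⱼ is the group difference in SD units at visit j. The article gives neither ρ nor the pattern of δⱼ, so the values below are assumptions that show the range (24 per group, alpha 5%).

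| Assumed difference at t1, t2, t3, t4 | ρ = 0 | 0.25 | 0.5 | 0.7 |
|---|---|---|---|---|
| 0, 1, 1, 1 (λ = 9/(1 − ρ)) | 70% | 83% | 95% | 99.8% |
| 0, 1, 0.5, 0.25 (λ = 6.56/(1 − ρ)) | 55% | 68% | 86% | 98% |

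The same d = 1 at t2 is compatible with power from 55% to almost 100%, according to inputs that are not stated.

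**The case against.** **The trial is not short of patients at its own assumption.** This stands. 24 exceeds both 14 and 17, and two-sided power at d = 1 is 92%, above the promised 80%. A reader who sees one-sided sizing next to two-tailed testing might infer that the trial is underpowered at d = 1. On a two-group comparison the figures show the opposite.

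**The calculation may have been made for the interaction.** This stands in part. The power section itself calls d = 1 the interaction effect, and the G*Power procedure is not named, so it cannot be said that the wrong test was powered. A condensed article may also leave software settings to the full protocol. That excuses a missing correlation. It does not excuse printing a set of inputs next to a result that they do not produce.

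**The two-tailed sentence might cover only other analyses.** It follows the passage on secondary outcomes and reliable change, but it is worded generally, and no one-sided test is reserved for the primary outcome.

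**The effect size is openly an assumption.** This stands. A reader might infer that d = 1 is too optimistic because the cited study's control arm was less intensive than E-TAU here. The article calls that comparator only TAU, and often uses the same word for its own E-TAU arm, so the inference cannot be checked. A reader might also take t1 to t2 as the primary contrast, but the article names change to t2, t3 and t4.

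**Conclusion.** The point holds as an error in the stated basis for the sample size, with three parts.

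- **Arithmetic.** 24 per group does not follow from d = 1, one-sided 5% and 80% power. The matching figure for a two-group comparison is 14, so the stated number is about 70% larger (24/14 = 1.71). This rests only on the printed inputs and the two-sample t-test.
- **Contradiction.** One-sided 5% in the power section conflicts with two-tailed 0.05 in Statistical analyses. It needs no assumption.
- **Insufficient inputs.** One d, one alpha and one power cannot give power for the time × intervention interaction. The ranges shown for that test depend on assumed correlations, time patterns and compound symmetry, and are illustrations only.

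The documents do not support the stronger claims that the trial is underpowered at d = 1 or that the calculation was made for a different test. The harm is that readers are given the wrong yardstick for a null result.

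**What to change.** Enrolment stays as it is. In the power section:

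1. Delete the one-sided qualifier and use two-sided 5% throughout.
2. Name the G*Power procedure and list every input, including the number of measurements and their assumed correlation, so that it matches the interaction test in Statistical analyses.
3. Correct whichever of d, power or n is misreported. Only the investigators can tell which it is.
4. Describe d = 1 as an assumption obtained by subtracting two within-arm pre-post effects (1.72 − 0.71).

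If the original G*Power run cannot be recovered, items 2 and 3 can be replaced by a detectable effect, for example: *For a two-group comparison at two-sided 5% and 80% power, the detectable difference is d = 0.83 with 24 per arm and d = 0.74 with 30 per arm; these are two-group values and not power for the time × intervention interaction.*

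The cost is one rewritten paragraph, recorded as an amendment and in the final report, as the Statistical analyses section already provides for deviations. No extra patients are needed. The two-sided statement is somewhat less favourable than the one-sided one: with 24 per arm the detectable d is 0.83 instead of 0.73.
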